## Abstract

**Background:**

Many glaucoma patients do not adhere to their medication regimens because they fail to internalize the (health) costs of non-adherence, which may not occur until years or decades later. Behavioural economic theory suggests that adherence rates can be improved by offering patients a near-term benefit. Our proposed strategy is to offer adherence-contingent rebates on medication and check-up costs. This form of value pricing (VP) ensures that rebates are granted only to those most likely to benefit. Moreover, by leveraging loss aversion, rebates are expected to generate a stronger behavioural response than equivalent financial rewards.

**Methods/Design:**

The main objective of the Study on Incentives for Glaucoma Medication Adherence (SIGMA) is to test the VP approach relative to usual care (UC) in improving medication adherence. SIGMA is a randomized, controlled, open-label, single-centre superiority trial with two parallel arms. A total of 100 non-adherent (Morisky Medication Adherence Scale ≤6) glaucoma patients from the Singapore National Eye Centre are block-randomized (blocking factor: single versus multiple medications users) into the VP and UC arms in a 1:1 ratio. The treatment received by VP patients will be strictly identical to that received by UC patients, with the only exception being that VP patients can earn either a 50 % or 25 % rebate on their glaucoma-related healthcare costs conditional on being adherent on at least 90 % or 75 % of days as measured by a medication event monitoring system. Masking the arm allocation will be precluded by the behavioural nature of the intervention but blocking size will not be disclosed to protect concealment. The primary outcome is the mean change from baseline in percentage of adherent days at month 6. A day will be counted as adherent when the patients take all their medication(s) within the appropriate dosing windows.

**Discussion:**

This trial will provide evidence on whether adherence-contingent rebates can improve medication adherence among non-adherent glaucoma patients, and more generally whether this approach represents a promising strategy to cost-effectively improve chronic disease management.

**Trial registration:**

NCT02271269. Registered on 19 October 2014.

**Electronic supplementary material:**

The online version of this article (doi:10.1186/s13063-016-1459-1) contains supplementary material, which is available to authorized users.

## Background

### Rationale

Glaucoma refers to a group of eye conditions that lead to damage to the optic nerve, which carries information from the eye to the brain. If uncontrolled, glaucoma first causes peripheral vision loss and eventually can lead to blindness. Glaucoma affects approximately 60 million people worldwide and is one of the leading causes of irreversible blindness [1]. In Singapore, glaucoma, affects roughly 3 % of those over age 40 and the total number of cases is growing due to Singapore’s ageing population [2, 3]. The most important modifiable factors of visual field loss in glaucoma are peak intraocular pressure (IOP), average IOP and fluctuations in IOP [4–7]. The majority of patients with glaucoma or suspected glaucoma are initially managed by IOP-reducing single or multi-drug treatments consisting of topical eye drops. This could be followed by surgical treatment for those whose IOP is not adequately controlled via medications [8, 9].

Correct use of medicated eye drops reduces IOP, subsequently slowing visual field loss for nearly 90 % of patients [10–13]. Despite the effectiveness of topical medication in controlling disease progression, roughly two-thirds of patients report some level of medication non-adherence to their medication [14–16]. Interventions to enhance medication adherence often focus on one or a combination of four strategies: simplification, education, social support and behaviour modification [17]. Most simplification interventions focus on reducing the number of doses per day, perhaps through extended-release capsules, or the number of medications [17]. Simplifying dosage requirements has consistently been shown to improve adherence [17–19]. However, there is evidence of non-adherence amongst glaucoma patients taking only one topical medication [20]. Education and social support interventions aim to increase adherence through greater knowledge transfer and increased self-efficacy. Education and social support interventions have shown some evidence of effectiveness in the short term, but results are less compelling in the long term [21, 22]. Behavioural interventions cover a wide range of strategies, such as pill organizers, reminder systems, and tailored regimens [17]. These studies too have shown mixed results, with both positive and negative results relating to the effectiveness of reminders, and no agreement on which behavioural intervention works best [23–26]. In a review of randomized control trials that seek to improve medication adherence, those that were most effective were multi-faceted, and included combinations of convenience, education, reminders, and reinforcement [19]. However, even the most effective interventions reviewed did not lead to large improvements in adherence. As a result, other strategies are needed.

Behavioural economics theory suggests that an important factor of non-adherence is that patients do not perceive a clear cause-and-effect relationship between non-adherence and the increased likelihood of disease progression, which may not occur until well into the future [27, 28]. As a result, many patients do not internalize the consequences of non-adherence until it is too late. One strategy to rectify this problem is to provide a short-term reward for increased adherence. Giuffrida et al. [29] reviewed 11 randomized incentive trials conducted in the United States where patients were paid either cash, gifts or vouchers for meeting adherence targets to various treatments and health services. These rewards, which ranged in value from USD5 to nearly USD1000, showed improve adherence in 10 out of the 11 studies reviewed. However, none focused on glaucoma patients and results varied widely across studies, suggesting that more research is needed to identify an optimal strategy to cost-effectively improve medication adherence [30].

In this trial we test a novel approach to improve medication adherence among glaucoma patients. The approach consists of adherence-contingent rebates on medication and check-up costs that are granted only when adherence goals are met as verified by a medication event monitoring system. Given that prescription refills and follow-up clinic visits occur regularly, the rebates provide a tangible and near-term benefit resulting from medication adherence. This strategy, which has been suggested by Loewenstein and colleagues [31], can be seen as a novel form of value pricing (VP) in the context of value-based insurance designs [32]. With standard value-based insurance designs, the co-payment for clinically effective treatments is reduced in efforts to increase their utilization. With our intervention design, incentives are allocated to medications that have not only been shown to be clinically effective, but that are also being effectively used by the patient, which represents a better use of resources. Another important feature of our approach is that incentives are provided in the form of rebates on costs already incurred by the patient. By offering a rebate that avoids a loss, as opposed to an equally sized reward, loss aversion theory predicts that this approach is likely to have a greater behavioural response [33].

This trial will provide evidence on whether adherence-contingent rebates can improve medication adherence among non-adherent glaucoma patients. Secondary objectives are to determine whether IOP and quality of life can also be improved, and whether the intervention represents a promising strategy to cost-effectively improve glaucoma management. Finally, explanatory analysis will aim at uncovering factors that might moderate the intervention effect and explain medication adherence.

### Objectives

*Primary objective*: determine whether complementing usual care (UC) with adherence-contingent rebates according to a VP strategy is superior to UC alone in improving medication adherence between baseline and month 6.

*Secondary objective 1*: determine whether the IOP of patients in the VP arm improves more (or deteriorates less) than that of patients in the UC arm between baseline and month 6.

*Secondary objective 2*: determine whether the glaucoma-related (GQL-15) and generic health-related (EQ5D-5 L) quality of life of patients in the VP arm improves more (or deteriorates less) than that of patients in the UC arm between baseline and month 6.

*Secondary objective 3*: determine whether the incremental cost-effectiveness ratio (ICER) of VP compared to UC will be favourable relative to international benchmarks for cost-effectiveness.

### Explanatory analyses

(i)compare adherence levels and intervention effect according to different definitions (aspects) of medication adherence(ii)determine factors that might moderate the intervention effect on medication adherence and quality of life(iii)determine factors of medication adherence at baseline

## Methods

### Trial design

The Study on Incentives for Glaucoma Medications Adherence (SIGMA) trial is designed as a randomized, controlled, open-label, single-centre superiority trial with two parallel arms. A total of 100 non-adherent glaucoma patients will be block-randomized (blocking factor: single versus multiple medication users) into the UC and VP arms in a 1:1 ratio. Baseline assessment lasts 1 month, followed by a 5-month intervention. The primary outcome is medication adherence as recorded by an electronic medication container.

### Study setting and eligibility criteria

All patients will be recruited at the Singapore National Eye Centre (SNEC). Singapore is an island city-state that has a population of 5.5 million and which is one of the most densely populated countries in the world. Singapore is a multicultural country consisting of Chinese (76.2 %), Malay (15 %), Indian (7.4 %) and other (1.4 %) ethnicities. The most widely spoken languages in Singapore are English, Mandarin, Malay and Tamil. The vast majority of those who speak Malay and Tamil are also fluent in English.

SNEC is part of SingHealth, which is Singapore’s largest public healthcare group. Since 1990, SNEC has been providing a full range of high-quality eye care and is a referral centre for complex cases both nationally and internationally. With its research arm, the Singapore Eye Research Institute (SERI), SNEC also extensively engages in academic research. SNEC treats both high-income patients and low-income patients. All Singaporean citizens and permanent residents are entitled to government subsidies in case of referral, while low-income patients can benefit from additional subsidies through various government schemes. The study will be conducted in collaboration with Duke-NUS, which is part of the academic medical centre SNEC belongs to.

#### Inclusion criteria

Glaucoma patient taking at least one eye drop medicationLow medication adherence based on the 8-Item Morisky Medication Adherence Scale (MMAS) [34–36]Aged between 21 and 85 yearsSingaporean citizens or permanent residentsConversant in English or Mandarin

#### Exclusion criteria

Stage 4 (severe) or Stage 5 (end-stage) glaucoma according to the Glaucoma Staging System (GSS) based on the Humphrey Visual Field [37].Patients who are not independently instilling their medications all or most of the time.

### Study arms

In this study, patients learn about their arm allocation by phone 1 month after their enrolment. This is to collect 1 month of baseline data on medication adherence. The patients then remain in their respective study arm for a duration of 5 months. In both arms, a questionnaire and clinical assessment will take place at baseline and month 6.

During the baseline visit, the research optometrist takes note of the glaucoma medication dosing schedule (see Fig. 1) in the participant instruction booklet (see Additional file 1) to ensure a uniform presentation of adherence goals across participants. Medication adherence will be monitored during the whole 6-month period by means of electronic containers eCAPs™ (Information Mediary Corporation, Ottawa, ON, Canada). An eCAP™ is a medication event monitoring system with an inbuilt electronic tag which records the time whenever it is opened and closed. Each eye drop will be stored in separate vials with separate eCAPs™. At month 3, eCAPs™ are collected by a courier service, medication adherence is calculated for months 2 and 3 and the eCAPs™ are returned to the patients along with a short adherence report for that period (see Additional files 2 and 3). The next assessment period for medication adherence runs from months 4 to 6, and adherence calculation takes place after the patients returned their eCAPs™ at the month 6 study assessment. Patients also receive a call at the end of months 2 and 5 to verify that they understand their arm allocation and adherence goals, and that patients with multiple eye drops keep their medication in the assigned eCAP™.

**Fig. 1 Fig1:**
[figure not shown]
Glaucoma medication dosing schedule. Note: Window length is set at a minimum of 6 hours and a maximum of 8 hours in the morning, afternoon or evening

#### Arm 1: usual care (UC)

Patients attend routine check-ups with an ophthalmologist where they have glaucoma eye drops prescribed for them, which they then purchase at the SNEC pharmacy. The frequency of check-ups varies between patients depending on the severity of their condition. The decision is made by the ophthalmologist on how regularly patients should return for check-ups, ranging from 3 months to once a year. IOP and visual acuity are measured at every visit while visual field readings are taken annually. Non-adherent patients may also be offered glaucoma counselling if necessary. During a counselling session, a nurse delivers an educational component on effective glaucoma treatment. Counselling includes the following components: (i) understanding of glaucoma and visual field process with a focus on risk factors and symptoms, (ii) management and treatment of glaucoma, (iii) medications usage with practical advice on self-application of eye drops. In addition, the nurse counsellor determines a dosing schedule for each medication that accommodates the patient’s lifestyle and takes into account working hours. During this discussion, the nurse counsellor underlines the health risks raised by non-adherence to the medication regimen.

In order to properly identify the effect of value pricing, we brought the following deviations to usual care. First, a short adherence report will be sent to the participants as described above. Second, a non-contingent payment of SGD30 will be made to them at months 3 and 6. However, unlike VP patients, no financial incentive will be given when they are adherent to their medications.

#### Arm 2: value pricing (VP)

The treatment received by VP patients is strictly identical to that received by UC patients, with the only exception being that VP patients can earn rebates on their glaucoma-related healthcare costs contingent on being sufficiently adherent to their medications.

Adherence is measured as the percentage of days where the patients take all their medication(s) within the appropriate dosing windows for the day. According to this definition, if a patient fails to take a single dose during the corresponding window, the whole day is counted as non-adherent. This concept of adherent-day stresses the importance of complying to the medication regimen as a whole and to its schedule in efforts to limit detrimental IOP fluctuations.

Patients who achieve more than 90 % adherent days will receive a rebate amounting to 50 % of their glaucoma-related healthcare costs, and patients achieving between 75 % and 90 % of adherent days will receive a 25 % rebate. Glaucoma-related healthcare costs comprise the out-of-pocket healthcare expenditure of one clinic visit at SNEC and 3 months’ worth of glaucoma medications per assessment period. When calculating glaucoma-related healthcare costs, a lower limit of SGD36.50 (the price of a subsidized doctor visit at SNEC) and an upper limit of SGD240 will be applied for those patients who spend less or exceed these limits. This means that those who qualify for a 50 % rebate will receive a rebate amount comprised between SGD18.25 and SGD120 per assessment period. Note that the rebate amounts will be explained to the patient and written down in the participant instruction booklet by the research optometrist during the baseline visit. However, emphasis will be given to the rebate rate (i.e., 25 % or 50 %) in order to be consistent with a value-based insurance design. Rebate payment is made via ebanking but the amount earned is added on the medication adherence report in order to make it fully visible to the patient.

### Outcome measures

#### Primary outcome

Our primary outcome is the *mean change from baseline in percentage of adherent days at month 6*. A day will be counted as adherent when the patients take all their medication(s) within the appropriate dosing windows for the day. The percentage of adherent days during month 1 (baseline) and month 6 will be calculated for each patient and the difference in mean change between study arms will be tested. The primary outcome is directly incentivized in the VP arm and not incentivized in the UC arm. As a result, this outcome will appropriately capture the behavioural change induced by value pricing, if any.

#### Secondary outcomes

*Monthly mean change from baseline in percentage of adherent days at months 2 to 5* in order to monitor adherence trajectories before the study end point (month 6).*Monthly change from baseline in the proportion of patients with percentage of adherent days greater or equal to respectively 75 % and 90 % over the study period (i.e. from month 2 to 6)*. These outcomes are of interest as they are defined according to the adherence thresholds that VP patients need to meet in order to receive their financial incentives.*Mean change from baseline in IOP at month 6*.*Mean change from baseline in GQL-15* [38] *score at month 6* as a glaucoma-specific measure of quality of life.*Mean change from baseline in EQ-5D-5L* [39] *score at month 6* as a generic measure of quality of life.*Mean cost of financial incentives at month 6 in the VP arm. Individual cost of financial incentives will be calculated using the participants’ monthly glaucoma-related healthcare costs recorded at baseline and percentage of adherent days at month 6 (i.e. primary outcome).*

#### Explanatory outcomes

*Monthly mean change from baseline in percentage of days where all doses where taken irrespective of time at months 2 to 6.*Monthly mean change from baseline in percentage of doses taken within the appropriate dosing windows *at months 2 to 6*.Monthly mean change from baseline in percentage of doses taken irrespective of time *at months 2 to 6*.*Mean change from baseline in the 8-Item Morisky Medication Adherence Score* [34–36] *(MMAS) at month 6* as this score is used to identify patients with low adherence as part of the screening process. The MMAS scale has been validated by showing that it is a good predictor of anti-hypertensive pharmacy refill adherence [34] and blood pressure (BP) control [36]. The MMAS scale has been used to measure adherence in a wide variety of chronic conditions including glaucoma [40].*Brief Illness Perception Questionnaire* [41] *(BIPQ) score at baseline.**Specific subscale of the Beliefs about Medication Questionnaire* [42] *(BMQ) score at baseline.*

### Sample size

We chose to power the study to detect differences of ten percentage points in average monthly percentage of adherent days at 6 months between the two study arms. This effect size is sufficient to measure the effects reported by a majority of financial incentive studies [30] and is in line with a recent study that also used percentage adherence measured by electronic caps as primary end point [43]. In order to detect such effect size, a total of 100 participants is needed. This calculation assumes a two-sided statistical test of difference in means with a 5 % significance level and a power of 80 %. In addition, the standard deviation of the monthly percentage of adherent days is assumed to be no greater than 16.3 %, which is the maximum standard deviation in dose-rate adherence reported by Robin and colleagues [44]. Finally, attrition over the 6-month study is assumed to be no greater than 20 %.

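### The stated inputs require 105 to 108 participants, not 100, for 80% power, and the 16.3% SD ceiling comes from a different adherence measure.

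*Protocol article*

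**What the plan says.** The Sample size section of the protocol article gives a complete calculation. The target is "differences of ten percentage points in average monthly percentage of adherent days at 6 months between the two study arms". The test is a "two-sided statistical test of difference in means with a 5 % significance level and a power of 80" per cent. The SD of the monthly percentage of adherent days is taken to be "no greater than 16.3 %, which is the maximum standard deviation in dose-rate adherence" in a cited study. Last, "attrition over the 6-month study is assumed to be no greater than 20" per cent. From these the section concludes: "In order to detect such effect size, a total of 100 participants is needed". Trial design fixes the allocation "into the UC and VP arms in a 1:1 ratio".

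The endpoint is defined under Primary outcome: "A day will be counted as adherent when the patients take all their medication(s) within the appropriate dosing windows for the day". The value pricing arm description adds that one dose missed in its window makes the whole day non-adherent. The Explanatory outcomes section lists percentage of doses taken as a separate measure.

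The Primary analysis section plans an ordinary least squares model of change from baseline, with terms for arm, baseline adherence, change in daily doses and other baseline characteristics, and a t test on the arm term.

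**The concern.** Two things in the sample size paragraph do not hold together.

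First, all the inputs are printed, so the total can be checked, and 100 does not follow from them once 20% attrition is allowed for. This is not a detail left to an analysis plan: the article states inputs and a result, and they disagree.

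Second, the SD is presented as a ceiling for the endpoint, but its source is a ceiling for another quantity. The protocol itself treats percentage of doses taken and percentage of adherent days as different outcomes. A maximum observed for one does not bound the other.

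What is at stake is the power statement. A reader of a non-significant result would take it that a 10-point effect had been looked for with 80% power under cautious assumptions. The first problem lowers that figure slightly. The second leaves it without a basis for this endpoint.

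**Working it through.** **Inputs (Sample size; Trial design).** Difference 10 points; SD 16.3; two-sided alpha 5%; power 80%; attrition 20%; allocation 1:1; stated total 100.

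**Attempt to reproduce 100.**
- Normal formula: n per arm = 2 × (1.96 + 0.8416)² × 16.3² / 10² = 41.7, so 42 per arm and 84 evaluable.
- t test (noncentral t): 42.7, so 43 per arm and 86 evaluable.
- Allowing for 20% loss: 84 / 0.8 = 105; 86 / 0.8 = 107.5, so 108.
- A one-sided test does not explain the figure: 33 per arm, 66 / 0.8 = 82.5.

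The stated 100 is therefore 5 to 8 short.

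**Power that 100 randomised delivers.** 100 × 0.8 = 80 evaluable, 40 per arm.
- At SD 16.3, unadjusted: 78.3% (normal) or 77.3% (t test).
- With no attrition, 50 per arm: 86.6% or 85.9%.
- 100 randomised yields 84 evaluable only if attrition is at most 16%, and 86 only if it is at most 14%.

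**Effect of the planned baseline adjustment.** Adjusting for baseline adherence reduces the residual SD to about SD × √(1 − ρ²), where ρ is the correlation between month-1 and month-6 adherence. The documents give no ρ, so the values below are assumptions. At SD 16.3 and ρ = 0.26 the residual SD is 16.3 × √(1 − 0.0676) = 15.7, and power at 40 per arm is 80%.

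**Sensitivity to SD.** The documents give no SD for adherent days, so 20, 25 and 30 are assumptions. Power at 40 per arm (noncentral t, 10-point difference, gain from other covariates ignored):

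| SD | ρ = 0 (unadjusted) | ρ = 0.3 | ρ = 0.5 | ρ = 0.7 |
|---|---|---|---|---|
| 16.3 | 77% | 81% | 88% | 97% |
| 20 | 60% | 64% | 72% | 87% |
| 25 | 42% | 46% | 53% | 70% |
| 30 | 31% | 34% | 40% | 54% |

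The shortfall at SD 16.3 is 2 to 3 percentage points and disappears with modest adjustment. At SD 25 or more, no correlation in the table reaches 80%.

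**The case against.** The strongest reply is that the planned analysis is not the unadjusted test. The regression adjusts for baseline adherence expressly to gain efficiency, and at SD 16.3 a correlation of only about 0.26 brings power back to 80%. In addition, both SD and attrition are stated as upper limits, so the shortfall appears only when both bind together. These points stand, and they rule out one reading that a reader might infer: that the design cannot have 80% power. The documents do not show that. They do not rescue the paragraph as written, because it names a test of means, claims no gain from adjustment and gives no correlation.

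A reader might also infer how the error arose. Unrounded, 83.4 × 1.2 = 100.1, which is what results if the evaluable number is multiplied by 1.2 instead of divided by 0.8. The article does not show how attrition was applied, so this remains a guess, and the discrepancy does not depend on it.

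A third tempting reading is that the day measure must be more variable than the dose rate, so that 16.3 is shown to be too low. That depends on the level of adherence. With beta-distributed dose adherence, SD 16.3 and independent doses, a mean of 80% gives a day-measure SD of about 24 for two doses a day and 27 for three. A mean of 50% gives about 17 and 14. Correlated doses would change these figures, and with one dose a day the all-doses rule adds no spread. The documents give no mean adherence for these patients, who are selected for low self-reported adherence. The supported statement is that the ceiling has no basis for this endpoint, not that it is known to be exceeded.

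**Conclusion.** Wrong as written, in two respects of different weight.

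The total of 100 does not follow from the stated inputs; 105 (normal) or 108 (t test) does. At the plan's own limits, power for the unadjusted test is 77% to 78% instead of 80%. This is a small error, certain as arithmetic, and it may be offset by the planned adjustment.

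The SD ceiling is unsupported, because it belongs to dose-rate adherence and is applied to an all-or-none, in-window day measure. This is potentially the larger problem, but its size cannot be drawn from the documents. The lower powers in the table illustrate assumed SDs of 20 to 30 and do not estimate this trial's power.

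**What to change.** Keep the enrolment target and correct the statement:

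1. State that 100 randomised with 20% attrition gives 80 evaluable patients and about 77% power for the unadjusted t test at SD 16.3.
2. Remove the claim that the SD of adherent days is no greater than 16.3, and say that the figure comes from dose-rate adherence.
3. Give power for the planned baseline-adjusted model in a short table, with SDs from 16.3 to 30 and baseline correlations from 0 to 0.7.
4. Use the SD of month-1 adherent-day percentage, pooled over arms, as a partial guide to the plausible SD rows. Trial status reports 93 patients enrolled, and arm allocation is revealed only after the baseline month, so these data precede the intervention and need no split by arm. They give neither the month-6 SD nor the correlation, so the table must still span a range.

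The cost is a few sentences, one table and a slightly less favourable stated power. Enrolment, conduct and the primary analysis do not change.
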